### Follow-up

The patient’s wounds will be followed by a member of the department staff or research group with photo documentation on day 0, day 7, at definitive wound healing (removal of staples), 4 months postoperatively, and in case of major wound complication.

Follow-up from day 7 and further on will be performed in the outpatient regime, at Rigshospitalet, orthopedic department; patients will be convened through e-books (secure platform for digital postboxes), and, if necessary, transport will be provided.

Preoperative, after 4 months, and 1 year quality of life will be evaluated with European Quality of Life - 5 Dimensions (EQ-5D) [17]; furthermore, Musculoskeletal Tumor Society Score (MSTS) [18] and Toronto Extremity Salvage Score (TESS) [19] will be used to evaluate function 4 months and 1 year postoperatively depending on surgery location (Fig. 2).

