### Secondary study endpoints

Length of hospital stay, readmission to hospital for treatment of a wound complication, time to primary wound healing and removal of staples (ready for radiation therapy), deep infection, postoperative seroma development, MSTS [18], and TESS [19] 4 months and 1 year postoperatively; furthermore, quality of life will be evaluated with EQ-5D [17] preoperatively, at 4 months and 1 year.

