### Statistical analysis

Fisher’s exact test will be used for categorical variables.

Depending on if the data could be considered normally distributed or not, a *t*-test for unpaired data or Mann–Whitney *U* test will be used for continuous variables.

Kaplan-Meier survival analysis will be used for overall survival (with log-rank test for comparison of groups). In case of an assumption of a difference in time to delayed wound healing, competing risk analysis will be used to address differences between the groups with death and amputation as competing factors.

All analyses will be performed in accordance with the intention-to-treat principles.

Two-sided *p*-values below 0.05 will be considered statistically significant.

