### Calculation of sample size

In the study of O’Sullivan et al. [11], a major wound complication within 4 months postoperatively was identified in 16 out of 94 (17%) STS patients treated with surgery and postoperative radiation therapy. There exist no studies evaluating the effect of NPWT on wound complications after surgery for STS combined with postoperative radiation therapy. However, in retrospective studies, it was found that NPWT reduced the risk of wound complications from 47 to 8% (83% reduction) in patients with lower extremity STS treated with preoperative radiation [14] and from 27 to 7% (75% reduction) in patients undergoing hip and knee revision surgery [20].

In a study design with an 80% risk of avoiding type II error, a 5% risk of type I error, and an 80% wound complication risk reduction in a population similar to the study by O’Sullivan et al. [11], we will need to include 154 STS patients (77 in each group) in an RCT.

To make allowance for dropouts (since the follow-up period regarding the primary study endpoint is only 4 months = 120 days few dropouts are expected) during the study period, we plan to include 160 patients.

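### The unpaired test named for MSTS, TESS and EQ-5D cannot use earlier scores at 1 year and, unless missing scores are imputed, covers only patients with a 1-year score

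*Protocol article*

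**What the plan says.** The Statistical analysis section of the protocol article gives one rule for every continuous variable. It is an unpaired comparison of the two arms, parametric or rank-based according to whether the data look normal ("test for unpaired data or Mann–Whitney"). The same section states: "All analyses will be performed in accordance with the intention-to-treat principles".

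The functional and quality-of-life scores are repeated measurements. Under Follow-up, MSTS and TESS "will be used to evaluate function 4 months and 1 year postoperatively depending on surgery location". Under Secondary study endpoints, "quality of life will be evaluated with EQ-5D [17] preoperatively, at 4 months and 1 year".

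The only remark on retention is in Calculation of sample size. It supports raising 154 patients to 160 with the reason "since the follow-up period regarding the primary study endpoint is only 4 months = 120 days few dropouts are expected". The article does not discuss missing scores. Death and amputation are named as competing events, but only for wound healing.

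**The concern.** An unpaired two-sample test takes one number per patient from each arm. Applied to the 1-year score, it has no place for the 4-month score or for the preoperative EQ-5D, although both are collected and are informative about the 1-year value. A patient seen at 4 months but not at 1 year adds nothing to the 1-year comparison unless a value is imputed.

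Two things are at stake. The first is precision, because information already in the database goes unused. The second is bias. If patients with poor 4-month scores are less likely to return at 1 year, a comparison of those observed is a comparison of responders, and it can mislead when the arms lose different numbers. The reason given for expecting few dropouts stops at 120 days. The population has high-grade sarcoma, and the article itself plans an overall survival analysis, so some 1-year scores will be absent.

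**Working it through.** **The plan's own figure.** Inputs from Calculation of sample size: control risk 17% (16/94), 80% relative reduction, 80% power, 5% type I error; two-sided, from Statistical analysis.

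- p1 = 0.17, p2 = 0.17 × 0.2 = 0.034, difference 0.136, mean 0.102.
- n per arm = [1.96 √(2 × 0.102 × 0.898) + 0.842 √(0.17 × 0.83 + 0.034 × 0.966)]² / 0.136² = 76.6, so 77 per arm and 154 in total.

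This reproduces the stated number. It concerns the primary endpoint only. The dropout allowance is 6/160 = 3.75%, and no figure is given for 1 year.

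**Assumptions.** The article gives neither the proportion missing at 1 year (m) nor the correlation between the 4-month and 1-year scores (r). I take m = 10-25% and r = 0.6-0.8, with 80 per arm and every 4-month score known. Since MSTS and TESS depend on surgery location, 80 per arm is an upper limit for them.

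**Precision, scores missing at random with respect to everything.** In units of the score's variance, for one arm of n patients:

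- observed 1-year scores only: 1 / [n(1 − m)]
- using both visits: (1 − r²) / [n(1 − m)] + r² / n
- ratio of the second to the first: 1 − r²m

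| r | m | Ratio | Variance cut |
|---|---|---|---|
| 0.6 | 10% | 1 − 0.36 × 0.10 = 0.964 | 3.6% |
| 0.7 | 20% | 1 − 0.49 × 0.20 = 0.902 | 9.8% |
| 0.8 | 25% | 1 − 0.64 × 0.25 = 0.840 | 16.0% |

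In patients, with r widened to 0.5-0.8: at m = 10% the unimputed test has 72 per arm, and the two-visit model is worth 73.8 to 76.9. At m = 20% the figures are 64, and 67.4 to 73.4. The gain is about 2 to 9 patients per arm. The difference detectable with 80% power in the unimputed test, 2.802 × √(2/n), is 0.443 SD with 80 per arm, 0.467 with 72 and 0.495 with 64.

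**Missingness that depends on the 4-month score, same rule in both arms.** Simulation: 80 per arm, 4,000 trials per setting, true difference 0.30 SD at both visits, r = 0.6-0.8. The log-odds of a missing 1-year score rise by 0.8 for each SD that the 4-month score falls, which gives about 9-24% missing.

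- Observed 1-year scores only: mean estimate about 0.27-0.29 SD, so 0.01-0.03 SD too small.
- Both visits: about 0.30 SD.
- Variance ratio: about 0.87-0.98, a cut of about 2-13%.

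Taken with the table, the variance cut spans about 2-16%.

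**Dropout that differs by arm.** With 20% missing in one arm and 10% in the other, log-odds slope 1 per SD, no true difference and r = 0.5-0.8, the observed-scores comparison is off by 0.041 to 0.071 SD in favour of the arm that loses more patients. The two-visit estimate is off by 0.003 SD at most. With 15% missing in both arms, the observed-scores bias is about zero.

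In a second setup, with a true difference of 0.30 SD, r = 0.7 and more dropout among controls, observed scores gave about 0.24 SD and both visits 0.30 SD.

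**Against sampling error.** With 64 and 72 observed, the standard error of the difference is √(1/64 + 1/72) = 0.172 SD. A bias of 0.071 SD is 0.41 of that; a bias of 0.024 SD is about one seventh.

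**The case against.** The strongest reply is that the article never says patients without a 1-year score are left out. It does not mention missing scores, and their handling is commonly left to a full protocol or analysis plan, neither of which is shown. Imputation followed by a t-test or rank test would fit the wording. That stands. A reader might infer that the plan drops every patient who lacks a 1-year score, but the text does not support it. What the text does fix is the test, and no form of that test uses the earlier score directly.

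A reader might also infer that the plan contradicts its intention-to-treat statement. It does not. Comparing patients in the arm to which they were randomised is compatible with an unpaired test, and tension arises only if the test is run on observed scores.

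The size is also open to challenge. With similar dropout in both arms the bias is a small fraction of a standard error, and nothing in the article shows that dropout will differ by arm. Metastatic disease is excluded, and follow-up takes place in the department's own clinic with transport if needed; both should limit losses. This too stands, and it keeps the point minor.

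Last, a mixed model does not solve death. For a patient who died before 1 year it implies a score that does not exist. That is why deaths need separate reporting.

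**Conclusion.** The point holds in a limited form. The named method leaves collected information out of the 1-year comparisons of MSTS, TESS and EQ-5D. Without imputation it also restricts them to patients with a 1-year score, which fits poorly with the intention-to-treat statement. The argument for few dropouts does not extend to 1 year.

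The loss is modest: about 2-16% of the variance of the 1-year difference, and a bias of about 0.01-0.03 SD with similar dropout in both arms or about 0.04-0.07 SD with unequal dropout. These figures rest on assumed missingness, correlation and dependence of dropout on the 4-month score, none of which the article gives. They also assume that the 4-month score is available for all. Only secondary endpoints are touched; the primary endpoint and its sample size are unaffected. This is a desirable improvement, not a flaw that threatens the trial.

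**What to change.** In Statistical analysis, replace the rule for these three scores with one mixed model for repeated measures per score:

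- Terms for arm, visit and arm-by-visit, with preoperative EQ-5D as a covariate in the EQ-5D model.
- Every patient with at least one postoperative score is included, in the randomised arm.
- The arm difference with its 95% CI is reported at 4 months and at 1 year.
- Deaths are reported by arm beside these results, with a sensitivity analysis that ranks deaths worst.
- The unpaired t-test or rank test is kept as supportive.

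The cost is analysis wording, with no new data or visits. The model assumes that scores are missing at random given the observed ones, which is weaker than what an observed-scores test needs, and that they are approximately normal. Patients with no postoperative score still do not enter. Its 1-year estimate must not be read as a score for patients who have died.

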### Calculation of sample size

In the study of O’Sullivan et al. [11], a major wound complication within 4 months postoperatively was identified in 16 out of 94 (17%) STS patients treated with surgery and postoperative radiation therapy. There exist no studies evaluating the effect of NPWT on wound complications after surgery for STS combined with postoperative radiation therapy. However, in retrospective studies, it was found that NPWT reduced the risk of wound complications from 47 to 8% (83% reduction) in patients with lower extremity STS treated with preoperative radiation [14] and from 27 to 7% (75% reduction) in patients undergoing hip and knee revision surgery [20].

In a study design with an 80% risk of avoiding type II error, a 5% risk of type I error, and an 80% wound complication risk reduction in a population similar to the study by O’Sullivan et al. [11], we will need to include 154 STS patients (77 in each group) in an RCT.

To make allowance for dropouts (since the follow-up period regarding the primary study endpoint is only 4 months = 120 days few dropouts are expected) during the study period, we plan to include 160 patients.

## Discussion

The surgical intervention in both groups is equal and according to current standards; the only difference is the wound dressing.

The randomization is planned as block randomization with 8 in each block; furthermore, a stratification of over extremity/trunk wall and under extremities will be performed; this is due to minimizing the risk of selection bias.

### Risks, side effects, and disadvantages

We do not expect that the patients participating in the study will experience any special side effects or complications related directly to the specific use of NPWT or the standard wound closure. The dressing may for some patients give a mild skin irritation of the skin under the enclosed dressing or a slight discomfort with having to wear an occlusive dressing. Any transient skin irritation (i.e., resolves within 24 h following device use and requires no medical intervention) will not be classified as an adverse device effect. Some blistering formations have been reported in relation to total hip and knee replacement surgery but no more than patients with conventional dressing [7].

A retrospective study showed that NPWT reduced the risk of wound complications in patients with lower extremity STS treated with preoperative radiation, and the use of NPWT was not associated with an increased risk of local recurrence [14].

No risk or side effects are reported by the manufacturer when adhering to the user manual.

Prevena™ NPWT is used daily at the orthopedic department; it is a CE-classified and FDA-approved medical device, and due to use in the recommended field, approval from the Danish Medicines Agency is not necessary.

### Ethical considerations

The study is approved by the Scientific Ethical Committee of the Capital Region of Denmark (H-21013549) and the Danish Data Protection Agency (P-2021-150), and it is registered at clinicaltrials.gov (NCT04960332) before the inclusion of patients. All patients will receive both oral and written information before written informed consent to participate is obtained.

The regulation from data protection regulation and data protection agency will always be followed.

The significant use of the present study is new knowledge concerning the best way to treat a certain group of patients with deep-seated STS of an extremity or the trunk wall. Knowledge from our study will benefit society in general and optimize utilization of resources, in terms of the best treatment for future patients.

In case of serious adverse preliminary results, data will be analyzed, and if one of the treatments is found to cause significant critical problems compared to the other (*p* < 0.05), the study will be ended. The study is thus designed to minimize unnecessary risks to the patients.

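### The early-stopping rule applies an unadjusted p<0.05, in either direction, to an undefined outcome at an unlimited number of looks, so the stated 5% type I error is not guaranteed

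*Protocol article*

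**What the plan says.** The stopping rule stands in the protocol article under Ethical considerations. The trigger is "In case of serious adverse preliminary results, data will be analyzed". The trial then ends "if one of the treatments is found to cause significant critical problems compared to the other", with p<0.05 as the criterion. The section gives no number or timing of looks, no definition of a critical problem and no adjusted boundary. Because it refers to either treatment, it works in both directions.

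Two other sections set the error rate that the rule has to fit:

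- Statistical analysis: two-sided p-"values below 0.05 will be considered statistically significant". For the binary primary endpoint, Fisher's "exact test will be used for categorical variables".
- Calculation of sample size: the 154 patients rest on "a 5% risk of type I error, and an 80% wound complication risk reduction", with 80% power.

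The primary endpoint (Primary study endpoints) is itself a harm. It counts secondary surgery for the wound, invasive wound procedures without anesthesia, and readmission for wound care, within 120 days. The trial is not blinded (Study design; Randomization).

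**The concern.** A 5% type I error holds for one test at 0.05. Here the same 0.05 is available at every interim comparison and again at the end, and the comparisons are prompted by how the data already look. If the interim outcome overlaps with the primary endpoint, each look is another chance to cross 0.05 when the dressings do not differ.

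The direction matters too. A stop because conventional dressing has more wound complications is framed as protection, but its result is a trial ended in favour of NPWT. On an overlapping outcome it works as an efficacy stop with no adjustment. Few events are needed: at 20 per arm, 5 against 0 already gives Fisher p = 0.047. At stake are the validity of the 5% claim and the risk that a chance imbalance ends the trial before it answers its question.

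**Working it through.** **Inputs from the article.** Control rate 17%, "identified in 16 out of 94 (17%) STS patients"; relative reduction 80%, so 0.17 × 0.2 = 0.034 under NPWT; two-sided alpha 0.05; power 80%; 77 per group required, 80 per group planned; Fisher's exact test.

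**Assumptions, because the article is silent.** Critical problems are taken to be the primary endpoint. Looks are equally spaced, outcomes are treated as immediate, and each look and the final test use p<0.05.

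**Step 1: reproduce the sample size.** With pooled variance and no continuity correction, and mean rate (0.17 + 0.034)/2 = 0.102:

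n = [1.96 × √(2 × 0.102 × 0.898) + 0.8416 × √(0.17 × 0.83 + 0.034 × 0.966)]² / 0.136²

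= [1.96 × 0.4280 + 0.8416 × 0.4171]² / 0.0185 = 76.5, so 77 per arm and 154 in total.

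This matches the article exactly as a fixed design with a single two-sided 0.05 test. No alpha was set aside for interim looks.

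**Step 2: overall error under the null.** Binomial data were simulated with 17% in both arms and 80 per arm (400,000 runs). The ranges cover independent runs of the same set-up.

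| Interim looks before the final test | Chance of ever reaching p<0.05, Fisher |
|---|---|
| 0 | 3.0 to 3.1% |
| 1 (at 40 per arm) | 4.8 to 5.0% |
| 2 | 5.6% |
| 3 | about 7% |
| 7 (every 20 patients) | 8 to 9% |
| 19 (every 8 patients) | about 11% |

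Fisher's test is conservative at this rate, with a single-test size of about 3%. That slack absorbs roughly one look, and the excess over 5% appears from two looks onward. At an assumed null rate of 30%, one look gives 5.2% and three give 7.7%.

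**Step 3: how little evidence the boundary needs.** With equal arms and no events in one arm, the two-sided Fisher p-value for k events in the other is 2 × C(n,k)/C(2n,k). For n = 20 and k = 5 this is 2 × 15,504/658,008 = 0.047. For n = 40, p<0.001 needs k = 11 (p = 0.0004), since k = 10 gives 0.00103.

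**Step 4: what a stricter boundary changes at one look, 40 per arm (exact calculation).**

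| True rates | Crosses p<0.05 | Crosses p<0.001 |
|---|---|---|
| Design effect, 17% vs 3.4% | 37% | 2% |
| NPWT doubles the rate, 17% vs 34% (assumed) | 33% | 3.5% |

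One look at p<0.001 can add at most 0.1 points to the error of the final Fisher test: 3.1% + 0.1% = 3.2%, below 5%.

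**The case against.** The best defence is that this is a safety clause. It stands under Ethical considerations, is triggered only by adverse results, and is justified as limiting risk to patients. No other section links it to the primary endpoint. That endpoint also includes seroma aspiration without anesthesia, which few would call a critical problem. If the two outcomes are wholly separate, the primary test is not directly inflated. This stands, and it is why the inflation is conditional. It does not clear the rule: the text does not exclude the primary endpoint, and the section on risks expects little from either dressing beyond mild skin irritation or discomfort. Major wound complications are therefore a plausible reading of critical problems.

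A second defence is that a contingent analysis probably means no look or one look, and under Fisher's test one look stays at about 5%. This stands for a 17% null rate, but nothing in the text limits the looks to one.

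A third is that a condensed article may leave monitoring detail to the full protocol. That excuses silence on the timing of looks. It does not excuse a stated threshold of p<0.05 that conflicts with a stated 5% error.

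A reader might infer more than the documents support:

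- **Inflation to about 22%.** This appears for an uncorrected chi-square test with a look every 8 patients. The article plans Fisher's test and names no such schedule.
- **Near-continuous monitoring.** Looks are conditional on adverse results, and the endpoint takes 120 days, so frequent looks would have incomplete data.
- **A symmetric p<0.001 as the remedy.** If NPWT doubled the complication rate, the chance of crossing at 40 per arm would fall from 33% to 3.5%. A boundary meant to guard against a false efficacy claim should not be imposed on the harm direction.

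**Conclusion.** The concern holds in a conditional form. The article states a stopping rule at unadjusted p<0.05, in either direction, on an undefined outcome and with unlimited data-triggered looks. It also claims a 5% type I error from a design that reserves no alpha for them. If critical problems include the primary endpoint, the 5% is not guaranteed: about 5% with one look, 5.6% with two, 7% with three and up to about 11% with a look every 8 patients. No single inflated value can be asserted, because both the outcome and the number of looks are assumed. If the outcomes are separate, the remaining defect is that a chance imbalance at 0.05 on an undefined outcome can end the trial. Severity: should-fix.

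**What to change.** Amend the stopping rule under Ethical considerations, and reconcile it with Statistical analysis and Calculation of sample size:

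1. Name the outcome that counts as a critical problem, and say whether it includes the primary endpoint.
2. Set a small fixed number of planned comparisons, for example one after 80 patients have reached day 120.
3. For stopping because conventional dressing is worse, replace p<0.05 with a stringent boundary such as Haybittle-Peto, p<0.001. The final test can then stay at 0.05 and the sample size need not change.
4. Handle harm under NPWT as a separate safety review of serious events at any time. It should make no efficacy claim and not rest on an automatic p<0.05 trigger. Its boundary is for the sponsor to set.

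The cost is an amendment while recruitment is under way, to a commitment made in an ethics-approved study. An interim difference favouring NPWT will also rarely stop the trial early: at the design effect, about 2% instead of 37% at 40 per arm.

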## Trial status

Protocol version: 07.05.2021 Version 1.2

Recruitment: started

Anticipated completion of recruitment: December 2024

## Data Availability

All data will be kept in REDCap, but datasets used and/or analyzed during this current study will be available from the corresponding author on reasonable request.

